### Pilot studies

The sample size and stabilometric variables to be used in the study were defined in two independent pilot studies, as described below:

a) Sample description and characterization: pilot study 1. The sample was defined based on a pilot study involving eight women (mean age: 23.16 ± 3.61 years) with TMD, as diagnosed using the RDC/TMD (described in the Procedures subsection). The good reliability and reproducibility of EMG signal in the evaluation of the muscles of mastication [42-45] was the main criterion for the choice measure to calculate the sample size in the proposed study.Thus, the sample size was calculated considering the largest standard deviation (SD) and root mean square (RMS) of the normalized amplitudes of the EMG signal of the right and left masseter and temporal muscles. The data were collected during maximum intercuspation for eight seconds before (T0) and after five sessions of nonspecific mobilization (T1). Considering a statistical power of 0.80, the right temporal muscle determined the largest sample (13 individuals (T0 = 1.19; T1 = 1.08; SD = 0.14)). The sample will be made up of male and female individuals, between 18 and 36 years of age, selected based on the eligibility criteria and diagnosed with TMD based on the RDC/TMD.

b) Stabilometric analysis: pilot study 2 after the definition of the sample size, a second pilot study was conducted to determine the stabilometric variables that exhibit the best within-day and between-day reproducibility. Fifteen female subjects with TMD, as diagnosed by the RDC/TMD (described in Procedures subsection), were recruited. The subjects had a mean age of 20.13 (± 6.19) years, mean height of 1.64 cm (± 0.06) and mean body weight of 61.08 Kg (± 9.72). Each participant completed two test sessions on two different days. All sessions were performed in the same laboratory environment by the same examiners, with a seven-day interval between sessions. Each session consisted of two successive trials of quiet upright stance, with a rest period of approximately 60 seconds between trials. The stabilometric data were recorded for 70 seconds under two visual conditions: eyes open (EO) and eyes closed (EC). For the analysis of the stabilometric variables, the initial 10 seconds were discarded to avoid initial transients and anticipation effects. Two collections were carried out under each visual condition, with a one-minute rest between collections (session 1). The order of the visual conditions (EO and EC) was randomly determined to control for the learning effect.

c) The justification for two collections under each visual condition is based on the fact that three trials were initially planned for each visual condition, but the first five individuals selected for this initial study reported discomfort and fatigue. Thus, new tests were carried out with the same participants with a one-day interval and the trials were reduced to two under each visual condition, with no report of any discomfort. The possibility of diminishing the time to less than 60 seconds was not considered due to the indication of using at least 90 seconds of data collection for each trial [46]. Moreover, it has been demonstrated that, under the eyes closed condition, reliability is lesser for short sampling and rises as the individual adapts [47]. Thus, the measurements of center of pressure (CoP) of these five individuals were not considered and only two trials under each visual condition were performed in this pilot study to maintain the integrity of the participants in the study.The tests were repeated after a one-week interval (session 2). All details regarding the equipment and analysis of the stabilometric data are described in the Procedures and Signal processing subsections, respectively.

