## Methods/Design

### Overview of research design

A randomized, controlled, blind, clinical trial is proposed to study the effects of specific and nonspecific mandibular mobilization. The participants will be allocated to three groups through a randomization process using opaque envelopes. Each group will receive a specific form of treatment for TMD. The control group (CG) will receive massage therapy and those submitted to joint mobilization will be divided into two groups: the specific mobilization group (SMG) and the nonspecific mobilization group (NMG). Evaluations will be carried out before and after treatment using the Research Diagnostic Criteria for Temporomandibular Disorders (RDC/TMD), EMG of the masseter and temporal muscles and stabilometry.

After screening, individuals with TMD (based on the RDC/TMD) will be selected. The study will be divided into three types of treatment, three evaluations and two phases, to which all individuals will be submitted:

Evaluation 1: randomization of treatment with allocation to treatment groups, stabilometric analysis and EMG analysis, with the administration of the protocol for the respective treatment.

Evaluation 2: second stabilometric and EMG evaluation immediately following respective treatment.

Treatment phase: treatment following respective protocol.

Evaluation 3: third stabilometric and EMG evaluation and second administration of the RDC/TMD questionnaire.

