#### ***Data analysis***

The Shapiro-Wilk test will be used to test the data with regard to Gaussian distribution. Data that demonstrate parametric distribution will be expressed as mean and standard deviation (SD) values. Data with nonparametric distribution will be expressed as median and inter-quartile interval. Either repeated-measure ANOVA or Friedman’s test will be used for the intra-group analysis and either one-way ANOVA or the Kruskal-Wallis test will be used for the inter-group analysis of data with parametric and non-parametric distribution, respectively.

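### The 0.80 power and the figure of 13 rest on a before-after change in one uncontrolled group, so they do not size the randomised three-arm comparison; whether 13 is per arm or total is not stated

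*Protocol article*

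**What the plan says.** Under Pilot studies, item a, the protocol article bases the sample on pilot data: "The sample was defined based on a pilot study involving eight women". On timing it says: "The data were collected during maximum intercuspation for eight seconds before (T0) and after five sessions of nonspecific mobilization (T1". The muscle needing the largest sample supplies the figure: "Considering a statistical power of 0.80, the right temporal muscle determined the largest sample (13 individuals". The inputs follow in brackets: "13 individuals (T0 = 1.19; T1 = 1.08; SD = 0.14". No alpha, sidedness, between-arm difference or pre-post correlation is given, and 13 is not labelled as per arm or total.

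The design is different. The Overview of research design says "The participants will be allocated to three groups through a randomization process using opaque envelopes", and the comparator is active: "The control group (CG) will receive massage therapy". Data analysis plans two things: an intra-group analysis by repeated-measures ANOVA or Friedman's test, and a between-group one, where "either one-way ANOVA or the Kruskal-Wallis test will be used for the inter-group analysis".

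**The concern.** The sizing data contain no comparator. A before-after change in one treated group says how many people are needed to detect that change within a group. It does not say how many are needed to detect a difference between randomised groups. A between-arm contrast of the same size carries sampling error from two groups, so at the same SD it needs about twice as many people in each arm.

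The trial's stated aim is to learn whether specific or nonspecific mobilization has an effect. Only the between-arm contrast separates such an effect from time, repeated testing and regression to the mean. If 0.80 is the only power figure on record, a null between-arm result may be read as good evidence of no difference when the comparison had a much lower chance of finding one. The comparator makes this harder: the Background section reports that massage of the masticatory muscles itself lowers EMG activity in TMD, which would shrink the between-arm difference.

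**Working it through.** **Inputs from the document (Pilot studies, item a).** Difference 1.19 − 1.08 = 0.11; SD 0.14; standardised difference 0.11/0.14 = 0.786; power 0.80; three arms (Overview of research design).

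**Assumed, because not stated.** Two-sided alpha 0.05, equal allocation, no dropout.

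**1. Reproducing the plan's figure.** The paired (one-sample) normal formula is n = [(1.96 + 0.84) × SD/difference]². Here (2.80 × 0.14/0.11)² = 12.7, rounded up to 13. Two-sample formulas do not return 13: they give 26 per arm (normal) or 27 per arm (t) two-sided, and 21 one-sided. With the paired t-test, 13 people give power 0.74, and 15 are needed for 0.80.

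The paired formula is not the only route. A within-subject repeated-measures ANOVA with three groups and three evaluations, f = 0.786/2 = 0.393 and an assumed correlation of 0.5, gives 0.79 at N = 12 and 0.83 at N = 13. That is also a within-subject effect, so the conclusion is the same: the figure belongs to a before-after change.

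**2. Between-arm power if 0.14 is the SD of the compared outcome and the arms differ by 0.11.** The noncentrality of the two-sample t-test is 0.786/√(2/n).

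| Size | Noncentrality | Pairwise power (t) | Omnibus one-way ANOVA |
|---|---|---|---|
| 13 per arm | 0.786/√(2/13) = 2.00 | 0.49 | 0.50 (one arm differs); 0.39 (means 0, 0.055, 0.11) |
| 13 in total, 4 vs 4 | 0.786/√(2/4) = 1.11 | 0.16 | 0.16–0.17; 0.13–0.14 (groups of 4, 4 and 5) |

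At 13 per arm, the standardised difference detectable with 80% power is 1.145, which is 1.145 × 0.14 = 0.16 in the outcome's units, against the 0.11 used for sizing.

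**3. If massage achieves half the change.** The between-arm difference becomes 0.11/2 = 0.055, and pairwise power at 13 per arm is 0.16 (SD 0.14).

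**4. If 0.14 is a per-visit SD.** With pre-post correlation r, the SD of a change score is 0.14 × √(2(1 − r)), and the baseline-adjusted residual SD is 0.14 × √(1 − r²). Pairwise power for 0.11 at 13 per arm:

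| r | SD of change | Power, change scores | Adjusted SD | Power, baseline-adjusted |
|---|---|---|---|---|
| 0.25 | 0.171 | 0.35 | – | – |
| 0.5 | 0.140 | 0.49 | 0.121 | 0.60 |
| 0.7 | 0.108 | 0.70 | 0.100 | 0.77 |
| 0.75 | 0.099 | 0.78 | 0.093 | 0.83 |

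Under the paired formula, 13 follows if 0.14 is the SD of the paired difference, or equally if it is a per-visit SD with r = 0.5. The document does not report r or say which SD this is.

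**The case against.** The strongest reply is that the document never attaches 0.80 to the between-arm test. It ties the figure to before versus after, and Data analysis does plan an intra-group analysis, which such a calculation fits. This stands. A reader might infer that the protocol claims 0.80 for the randomised comparison, but the text does not say so. The defect is that the only sizing offered for a randomised trial covers the analysis that does not use the randomisation.

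Second, no between-arm difference was ever planned. The 0.11 came after five sessions, while the trial gives ten, so the true between-arm effect could be larger than 0.11, or smaller because the control is active. This also stands. A reader might take 49% or 16% as the trial's power. The documents support neither as a fact, because both depend on an assumed alpha, an assumed difference and an assumed meaning of 0.14. The mention of using the largest SD can be read as a per-visit SD, and Data analysis does not say whether the between-group ANOVA uses post-treatment values or changes.

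Third, one might infer that 13 is certainly the total, or certainly per arm. The text supports neither. One might also hold that only the paired formula yields 13. A within-subject repeated-measures calculation reaches it too, so the derivation is inferred.

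Finally, an article condenses its full protocol. That would excuse an omission, but here a power, a sample size and its inputs are printed, and they do not fit the three-arm comparison printed alongside them.

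**Conclusion.** The point holds as a mismatch between the sizing and the randomised comparison, not as an arithmetic error: 13 reproduces. The 0.80 describes a within-arm before-after change, and about 0.74 by the paired t-test.

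Under two-sided alpha 0.05, a between-arm difference of 0.11 and SD 0.14 for the compared outcome, the between-arm test has about 0.49 power at 13 per arm and about 0.16 if 13 is the total. With 0.14 as a per-visit SD, the 13-per-arm figure ranges from about 0.35 to 0.83 over correlations of 0.25 to 0.75. It exceeds 0.80 only with baseline adjustment at the highest correlation tried, and the document reports neither. Any reduction of EMG activity by massage that narrows the between-arm difference lowers these figures.

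**What to change.** Reword the sample-size paragraph, without adding patients:

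- The sponsor should state whether 13 is per arm or the total. The text does not settle it.
- Label the 0.80 as applying to the within-arm before-after change only, and name the formula actually used.
- For the actual size, state the between-arm power or the detectable between-arm difference, with the alpha, the meaning of the SD and the pre-post correlation assumed. At 13 per arm with SD 0.14 for the compared outcome, the detectable difference at 80% power would be 0.16.
- Make the between-arm contrast baseline-adjusted, using the EMG already recorded at Evaluation 1.

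The cost is a rewritten paragraph, a line in Data analysis and a less favourable stated power. The baseline adjustment needs no new measurement.

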### Signal processing

#### ***Stabilometric parameters***

Displacement from the center of pressure (CoP) in the anteroposterior (AP) and mediolateral (ML) directions will be used to analyze body sway, as in the preliminary study (pilot study 2). CoP data will be filtered with a Butterworth low-pass filter with a cut-off frequency of 10 Hz [46]. Postural sway will be quantified by means of two common scale-dependent variables: CoP sway area as an indicator for magnitude of CoP movements and CoP mean velocity and frequency as indicators of the efficiency of postural control. As an indicator for the regularity of CoP movements, a scale-independent variable denominated sample entropy (SaEn) will be used. Each parameter is briefly described below:

– Sway area (cm^2^) will be estimated by fitting an ellipse to the CoP data (AP versus ML) that encompasses 95% of the data; [48]

– Mean velocity (cm/s) of the CoP in both AP and ML directions will be calculated by taking the total distance traveled and dividing it by the time of the trial; [49]

– Frequency (Hz) of CoP displacement will be determined by the frequency at which 80% of the CoP spectral power is below. The 80% value was chosen based on the study by Baratto *et al*. (2002) [50], who suggest that this value is a better discriminator for CoP data than other spectral measurements;

– SaEn is a method for quantifying the regularity of a time series [51,52] and reflects the conditional probability that two sequences of 'm’ consecutive data points that are similar to each other will remain similar when one more consecutive point is included. Being 'similar’ means that the value of a specific measure of distance is less than 'r’. Therefore, SaEn is a function of m and r parameters [53]. The embedding dimension, m, and the tolerance distance, r, will be set to m = 3 and r = 30% of standard deviation of the data sequence [54]. To render an outcome for the scale-independent SaEn, the CoP data in both AP and ML directions will be normalized to unit variance by dividing the time-series in question by their respective standard deviation [55]. Values close to zero indicate greater regularity, while values closer to two indicate greater entropy in the signal being analyzed. In the present study, a decrease in sample entropy (that is, more regular sway fluctuations) will be interpreted as a decrease in the effectiveness of postural control.

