The weakest index regarding reliability was the SaEn, followed by sway area. The variation in ICC among poor, fair and good and the high SEM demonstrate that these variables should not be considered when investigating the possible effects of mandibular mobilization for the treatment of TMD.

The results of this pilot studied showed that mean velocity was the most reliable measure, which is consistent with earlier reports, and can be selected as a reliable postural sway measure. Moreover, the results of the proposed study will help determine whether specific and/or nonspecific mandibular mobilization exerts an effect on the muscles of mastication and postural control. Moreover, if an effect is detected, the methodology defined in the proposed study will allow identifying whether the effect is local (found only in the muscles of mastication), global (found only in postural control) or generalized.

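### Sway area and sample entropy remain among the trial's planned sway measures although the pilot run to choose those measures advised against both

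*Protocol article*

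**What the plan says.** The Pilot studies section of the protocol article opens by stating that "The sample size and stabilometric variables to be used in the study were defined in two independent pilot studies". For stabilometry it gives the selection criterion: "a second pilot study was conducted to determine the stabilometric variables that exhibit the best within-day and between-day reproducibility".

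The result is in the Discussion: "The weakest index regarding reliability was the SaEn, followed by sway area". The authors then conclude that "these variables should not be considered when investigating the possible effects of mandibular mobilization for the treatment of TMD", and name mean velocity as a reliable sway measure that may be chosen.

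The Stabilometric parameters section, under Signal processing, describes the trial differently. "Postural sway will be quantified by means of two common scale-dependent variables: CoP sway area as an indicator for magnitude of CoP movements", alongside mean velocity and frequency. "As an indicator for the regularity of CoP movements, a scale-independent variable denominated sample entropy (SaEn) will be used". It also fixes a reading, in terms of postural control: "In the present study, a decrease in sample entropy (that is, more regular sway fluctuations) will be interpreted as a decrease in the effectiveness of" that function.

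**The concern.** The pilot's stated job was to fix the list of stabilometric measures. It reached a verdict, and that verdict was not carried into the section that lists what the trial will compute and how it will be read. An analyst who follows Signal processing would test sway area and SaEn for a treatment effect. One who follows the Discussion would not.

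This matters because the article says that the design will allow an effect to be classed as local, global or generalized. The global part depends on whether postural control changed, and so on which centre-of-pressure measures count. Measures with low reliability dilute a real effect, and a null result on them does not separate absence of effect from measurement error. They also add tests behind the same conclusion without a reason that the authors themselves accept.

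**Working it through.** **1. The texts side by side.**

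- Pilot studies: the pilots define the trial's measures, and the criterion for stabilometry is reproducibility.
- Discussion: SaEn and sway area are rejected for studying the effect of mobilization; mean velocity is endorsed.
- Stabilometric parameters: sway area and SaEn are both planned, in the future tense, with an interpretation rule for SaEn.
- Data analysis names no stabilometric variable, so it does not settle the matter. Nothing elsewhere limits sway area and SaEn to the pilot.

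**2. Does the pilot's ranking reproduce?** Inputs are the Table 4 ICCs (three columns: session 1, session 2, sessions 1 and 2 together) and the bands in the Reliability section (poor below 0.40, fair 0.40 to 0.59, good 0.60 to 0.74, excellent from 0.75). Mean ICC = sum of cells / number of cells.

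| Measure | Mean, all cells | Range | Mean, between-day | Excellent cells |
|---|---|---|---|---|
| SaEn | 5.64/12 = 0.47 | -0.04 to 0.71 | 1.91/4 = 0.48 | 0 of 12 |
| Sway area | 3.48/6 = 0.58 | 0.44 to 0.81 | 1.00/2 = 0.50 | 1 of 6 |
| ƒ80 | 8.43/12 = 0.70 | 0.50 to 0.85 | 2.69/4 = 0.67 | 6 of 12 |
| Mean velocity | 10.79/12 = 0.90 | 0.76 to 0.98 | 3.33/4 = 0.83 | 12 of 12 |

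The order SaEn, area, ƒ80, velocity reproduces. The Discussion describes the ICCs of SaEn and area as poor to good; one area cell (eyes closed, session 1) is 0.81, which is excellent. The order does not change.

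**3. Between-day figures with their uncertainty.** These bear on Evaluation 3, which follows the treatment phase. They come from 14 analysed women (15 recruited, one removed) on log-transformed data. The last column is 1/ICC. If the ICC is the reliability of one reading, observed variance = true variance / ICC, so a comparison of groups on a single reading needs 1/ICC times the sample that an error-free measure would need.

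| Measure | Eyes open: ICC (95% CI) | Eyes closed: ICC (95% CI) | 1/ICC, open / closed |
|---|---|---|---|
| SaEn AP | 0.20 (-0.03 to 0.54) | 0.54 (0.27 to 0.78) | 5.00 / 1.85 |
| SaEn ML | 0.67 (0.44 to 0.86) | 0.50 (0.22 to 0.77) | 1.49 / 2.00 |
| Sway area | 0.52 (0.26 to 0.78) | 0.48 (0.21 to 0.74) | 1.92 / 2.08 |
| ƒ80 AP | 0.76 (0.56 to 0.90) | 0.66 (0.43 to 0.85) | 1.32 / 1.52 |
| ƒ80 ML | 0.70 (0.46 to 0.86) | 0.57 (0.31 to 0.80) | 1.43 / 1.75 |
| Velocity AP | 0.79 (0.58 to 0.91) | 0.76 (0.53 to 0.89) | 1.27 / 1.32 |
| Velocity ML | 0.96 (0.91 to 0.98) | 0.82 (0.65 to 0.93) | 1.04 / 1.22 |

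The multipliers are rough. For area, eyes open, the interval runs from 1/0.78 = 1.28 to 1/0.26 = 3.85. For SaEn AP, eyes open, the lower limit is negative, so there is no upper bound. The article does not say whether the ICCs refer to single or averaged readings.

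**4. How many measures are affected.** Counting rows of Table 4: area 2, velocity 4, ƒ80 4, SaEn 4, in all 14. Following the Discussion removes 2 + 4 = 6 and leaves 8.

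**The case against.** The best defence is that Stabilometric parameters serves two purposes. The Pilot studies section sends the reader to Signal processing for the details of the pilot's own analysis, so area and SaEn had to be defined there whatever the pilot found. That is true, but it does not remove the conflict. The pilot is reported in the past tense and this section is written in the future. It says that centre-of-pressure displacement "will be used to analyze body sway, as in the preliminary study (pilot study 2"), which sets the trial apart from the pilot. A rule that a fall in SaEn means poorer postural control also has no use in a test-retest study that gave no treatment.

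A second defence is that the Discussion already answers the question: it is the specific conclusion of the study meant to choose the measures, so a careful reader would drop both. This stands in part. A reader might infer that the trial will base its postural conclusions on rejected measures. The document does not establish that; it leaves open which section prevails. Nor does it label any stabilometric measure primary or secondary.

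Third, the reliability contrast is not uniform. Evaluation 2 comes straight after the first treatment, where within-day ICCs apply, and there area reaches 0.81 (eyes closed, session 1) and 0.72 (eyes open, session 2). SaEn ML with eyes open (0.67 between days) is slightly above ƒ80 AP with eyes closed (0.66) and clearly above ƒ80 ML with eyes closed (0.57). This stands, and it is why the case rests on the authors' own conclusion rather than on a cut-off applied here.

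Fourth, a reader might turn the count of measures into a false-positive rate: 1 - 0.95^14 = 0.51 falling to 1 - 0.95^8 = 0.34. The document does not support this. No significance level is stated, the measures come from the same recordings and cannot be taken as independent, and 14 is not the number of tests, since within-group and between-group analyses are planned over three groups and three evaluations. Low reliability itself costs power; it does not raise the type I error of a test.

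**Conclusion.** The contradiction holds and rests on the text alone. The pilot was run to select the trial's stabilometric measures, its conclusion excludes SaEn and sway area for the trial's own question, and the section defining the trial's measures keeps both and says how one of them will be interpreted. The pilot figures bear out the authors' ranking.

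In size, 6 of the 14 planned stabilometric measures are affected. Their between-day ICCs run from 0.20 to 0.67, against 0.76 to 0.96 for mean velocity and 0.57 to 0.76 for ƒ80, all estimated imprecisely. The main consequence is diluted effects and null findings that cannot be interpreted well; the lesser one is extra tests behind the global-effect conclusion.

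Two further inferences are not supported. One is that the plan is arranged so that any significant sway measure can be reported: nothing says so, and the same remark would apply to the eight measures left. The other is that the pilot places ƒ80 below velocity as a formal secondary measure: the article ranks velocity as most reliable but assigns ƒ80 no role.

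**What to change.** Reconcile Stabilometric parameters with the Discussion before the analysis; the trial is still recruiting.

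- Remove sway area and SaEn, with the SaEn interpretation rule, from the measures used to judge the treatment effect, or state that they are descriptive only.
- Name mean velocity (AP and ML) as the stabilometric measure on which the postural-control conclusion rests.
- Have the investigators state whether ƒ80 is kept and at what rank.
- If the definitions of area and SaEn are needed to document pilot study 2, keep them and say that this is their purpose.

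The change is to text only and needs no new data or procedure. The cost is the loss, as evidence of effect, of two measures that the authors already advise against.
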